# Thrombus Aspiration in ThrOmbus containing culpRiT lesions in Non-ST-Elevation Myocardial Infarction (TATORT-NSTEMI): study protocol for a randomized controlled trial

**DOI:** 10.1186/1745-6215-14-110

**Published:** 2013-04-25

**Keywords:** Non-ST-elevation myocardial infarction, Thrombectomy, Cardiac magnetic resonance imaging, Microvascular obstruction

## Abstract

**Background:**

Current guidelines recommend thrombus aspiration in patients with ST-elevation myocardial infarction (STEMI); however, there are insufficient data to unequivocally support thrombectomy in patients with non-STEMI (NSTEMI).

**Methods/Design:**

The TATORT-NSTEMI (Thrombus Aspiration in ThrOmbus containing culpRiT lesions in Non-ST-Elevation Myocardial Infarction) trial is a prospective, controlled, multicenter, randomized, open-label trial enrolling 460 patients. The hypothesis is that, against a background of early revascularization, adjunctive thrombectomy leads to less microvascular obstruction (MO) compared with conventional percutaneous coronary intervention (PCI) alone, as assessed by cardiac magnetic resonance imaging (CMR) in patients with NSTEMI. Patients will be randomized in a 1:1 fashion to one of the two treatment arms. The primary endpoint is the extent of late MO assessed by CMR. Secondary endpoints include early MO, infarct size, and myocardial salvage assessed by CMR as well as enzymatic infarct size and angiographic parameters, such as thrombolysis in myocardial infarction flow post-PCI and myocardial blush grade. Furthermore, clinical endpoints including death, myocardial re-infarction, target vessel revascularization, and new congestive heart failure will be recorded at 6 and 12 months. Safety will be assessed by the incidence of bleeding and stroke.

**Summary:**

The TATORT-NSTEMI trial has been designed to test the hypothesis that thrombectomy will improve myocardial perfusion in patients with NSTEMI and relevant thrombus burden in the culprit vessel reperfused by early PCI.

**Trial registration:**

The trial is registered under http://www.clinicaltrials.gov: NCT01612312.

## Background

Use of manual thrombectomy devices during percutaneous coronary intervention (PCI) in patients with acute ST-elevation myocardial infarction (STEMI) has been shown to decrease the incidence of cardiac death and repeat myocardial infarction [1-3]. Consequently, current guidelines of the European Society of Cardiology (ESC) and the American Heart Association/American College of Cardiology (AHA/ACC) recommend manual thrombectomy in patients with STEMI (class IIa, level of evidence A, and class IIa, level of evidence B, respectively) [4,5]. However, approximately 50 to 70% of all patients with non-ST-elevation myocardial infarction (NSTEMI) also display a relevant thrombus burden in the culprit vessel [6,7]. Furthermore, with rates of angiographic no-reflow phenomenon ranging from 15 to 40%, depending on thrombus burden and intra-procedural thrombotic events, only suboptimal reperfusion success can be achieved in a significant portion of patients with NSTEMI [8-10]. Thus, thrombectomy in patients with NSTEMI may represent a useful intervention, with the potential to improve patient prognosis. However, current guidelines do not give a clear recommendation for thrombus aspiration in NSTEMI [11,12]. This is mainly because of the lack of data on thrombus aspiration in NSTEMI, as only one small prospective observational study has been published to date [7]; in that 70-patient study, thrombectomy had a similar effectiveness rate to that reported in patients with STEMI.

This emphasizes the need for an adequately powered randomized controlled trial (RCT) to address the current role of thrombus aspiration in patients with NSTEMI and a relevant thrombus burden in the culprit vessel. The TATORT-NSTEMI (Thrombus Aspiration in ThrOmbus containing culpRiT lesions in Non-ST-Elevation Myocardial Infarction) trial is designed to test the hypothesis that against a background of early revascularization, adjunctive thrombectomy leads to less microvascular obstruction (MO) compared with conventional PCI alone, as assessed by cardiac magnetic resonance imaging (CMR).

## Methods/design

The TATORT-NSTEMI trial is a prospective, multicenter, randomized, controlled, open-label study to compare PCI plus routine thrombus aspiration with PCI without thrombus aspiration in patients with NSTEMI and relevant thrombus burden who are undergoing early invasive reperfusion therapy. The study will determine if adjunctive thrombectomy is superior than PCI alone with respect to the extent of no-reflow/MO assessed by CMR in patients with NSTEMI.

### Primary and secondary endpoints

The primary study endpoint of the TATORT-NSTEMI trial is the extent of late MO assessed by CMR on days 1 to 4 after randomization. Using CMR, zones of MO within the infarcted myocardium can be visualized and quantified, representing the CMR equivalent of the no-reflow phenomenon [13,14]. MO assessed by CMR has not only been shown to be associated with adverse functional outcome after myocardial infarction [15,16], but also with adverse clinical outcome including mortality [17-19]. Further, late MO assessed 15 minutes after contrast-medium injection has been shown to have higher prognostic impact than early MO assessed 1 to 2 minutes after gadolinium administration or by first-pass gadolinium-enhanced perfusion [17,20]. The mechanistic hypothesis of the current trial is that thrombus aspiration will result in reduction of distal embolization, thus preserving microvascular integrity, reflected by less late MO, which will translate into improved clinical outcome.

Secondary endpoints include other CMR parameters associated with patient prognosis, such as early MO, infarct size, myocardial salvage, and left ventricular ejection fraction (LVEF), as well as angiographic markers of reperfusion success such as the thrombolysis in myocardial infarction (TIMI) flow post-PCI and myocardial blush grade [18,21]. In addition, troponin T after 24 and 48 hours for determination of enzymatic infarct size will be evaluated. Further, a combined clinical endpoint including death, re-infarction, target vessel revascularization, and congestive heart failure (CHF) will be assessed after 6 and 12 months. Death is defined as death from any cause, but will be divided into cardiac and non-cardiac causes, and will be regarded as cardiac in origin unless obvious non-cardiac causes can be identified. The diagnosis of re-infarction during the index hospitalization will be based on clinical symptoms, new ST-segment changes, and an increase in the creatine kinase-MB levels above the reference limits in patients with normalized values, or if there is an increase of more than 20% from the most recent non-normalized measurement. At follow-up, any new ischemic symptoms leading to hospital admission accompanied by raised troponin levels will be defined as re-infarction [22]. New CHF after randomization during hospital stay will be defined as CHF when there is at least one of the following conditions and it requires treatment with diuretics (cardiogenic shock, pulmonary edema, or signs of pulmonary congestion on X-ray, rales of greater than one-third from lung basis, pulmonary capillary wedge pressure >25 mmHg, or dyspnea with blood oxygen saturation <90% in the absence of lung disease). After hospital discharge, any new CHF leading to re-hospitalization will be counted. Clinical outcome will be assessed by a telephone interview at 6 and 12 months. Any clinical event will be verified by hospital or general practitioner records. Finally, assessment of quality of life will be performed using the EuroQol-5D (http://www.euroqol.org) questionnaire during the 6-month and 12-month follow-ups.

Safety assessment will include stroke and bleeding until hospital discharge. Stroke will be defined as any new neurological symptoms in association with signs of ischemia or hemorrhage in cranial computed tomography or magnetic resonance imaging. Bleeding will be defined in accordance with the GUSTO (Global Utilization of Streptokinase and t-PA for Occluded Coronary Arteries) criteria as 1) severe or life-threatening, 2) moderate, or 3) mild bleeding [23]. However, based on previous studies, thrombus aspiration is associated with only modest complications, therefore no major safety concern for thrombus aspiration is expected. All safety aspects will be monitored by a Data Safety Monitoring Board (DSMB). All clinical and safety endpoints will be adjudicated by a Clinical Endpoints Committee (CEC) blinded to treatment assignment, based on data provided by the clinical-trial sites.

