### Patient population

The study population will consist of 460 patients with NSTEMI enrolled at eight centers in Germany. Informed consent will be required prior to randomization.

Patients will be eligible for the study if they have: 1) ischemic symptoms such as angina pectoris for more than 20 minutes; 2) occurrence of previous symptoms less than 72 hours before randomization; 3) cardiac troponin levels above the 99th percentile; and 4) culprit lesion containing thrombus (TIMI thrombus grade 2 to 5 within the lesion) and intended early PCI.

Exclusion criteria will be presence of cardiogenic shock, STEMI, no identifiable culprit lesion, coronary morphology ineligible for thrombectomy (for example, very tortuous vessels or severe calcification), indication for acute bypass surgery, age less than 18 or more than 90 years, pregnancy, current participation in another clinical study, co-morbidity with limited life expectancy of less than 6 months or contraindications to CMR at study entry (for example, severe claustrophobia, implanted pacemakers or defibrillators, relevant metallic implants, known allergy to gadolinium, severe renal failure with creatinine clearance <30 ml/h), and contraindications for treatment with heparin, aspirin, or thienopyridines.

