### Randomization and patient treatment

Patient randomization will be performed centrally, with a randomization ratio of 1:1 (n = 230 patients per group; see Figure 1 for study flow) using an internet-based randomization program. No stratification will be performed. All participating hospitals are high-volume tertiary care centers with experienced cardiologists performing all interventions. Manual thrombectomy will be performed in the thrombus aspiration group with an aspiration catheter commonly used in daily clinical routine (Eliminate^®^; Terumo Europe, Leuven, Belgium). In the standard PCI group, patients will be treated by conventional PCI in accordance with local practice without thrombectomy. Cross-over is not planned; however, if this occurs, the reasons will be recorded. Manual thrombectomy will be the only difference between the groups, and all other therapeutic procedures will be similar in both treatment arms.

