In the intervening time, two other studies on MO and NSTEMI were published, which reported a lower prevalence and extent of MO than expected [20,32]. Thus, the Steering Committee decided to perform a preliminary analysis on CMR parameters, including the first 60 patients enrolled in TATORT-NSTEMI. A prevalence of MO of approximately 40% with a median extent of 1.0%LV was oberserved. We thus decided to critically revise our sample-size calculation and adapt it based on the new available data and the preliminary analysis. We now expect an absolute difference in the primary endpoint (late MO) of 0.5%LV between the two treatment groups with a mean extent of 1.0%LV for late MO in the whole study cohort [20,32]. This difference is judged as clinically relevant [17,20,26,27,31]. A standard deviation of 1.8%LV is assumed [17,20,26,27,31,32]. Based on α = 5%, a two-sided hypothesis test, and a statistical power of 80%, 204 patients per group are needed to reject the null hypothesis of no difference between groups. On the basis of clinical experience and data in STEMI, it is further expected that it will not be possible to perform thrombectomy for 5% of all patients in the thrombectomy group, and that 10% of all patients, either will not undergo a CMR examination or their CMR images will be of insufficient quality for analysis [17,26,27]. This will result in a sample size of 2 × 230 randomized patients per group. We thus decided to include 60 additional patients after critical revision and adaptation of our initial sample-size calculation. This protocol modification was approved by the central ethics committee at the University of Leipzig. Sample-size calculation was performed using SigmaStat software (Version 3.5; Systat Software Inc., Chicago, IL, USA).

Pre-specified subgroup analyses by gender, presence of diabetes, TIMI thrombus burden (2 to 4 versus 5), TIMI flow pre-PCI (0 to 1 versus 2 to 3), and time from most recent symptoms to occurrence of PCI (<6 versus ≥6 hours), and additional administration of glycoprotein IIb/IIIa inhibitors will be performed.

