All patients will be analyzed on an intention-to-treat basis. The differences in primary and secondary endpoints between the treatment groups will be assessed using an unpaired *t*-test. In addition, as a secondary analysis, the differences between the treatment groups in the main outcome will be assessed using an unpaired *t*-test adjusted by baseline values (ANCOVA). Categorical variables will be analyzed by Fisher’s exact test. The 95% confidence interval (CI) for differences in quantitative data will be displayed. For clinical events, relative risks and 95% CI will be reported. To identify factors associated with the observed results, univariate and multivariate regression analysis will be performed. To assess clinical outcome, Kaplan-Meier curves with log-rank comparison and Cox regression analyses will be performed. A two-tailed *P*-value of <0.05 will be considered significant.

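### Troponin T at 24 and 48 hours is compared without adjustment for entry troponin or symptom delay; the test is valid but gives up precision

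*Protocol article*

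**What the plan says.** All references are to the protocol article.

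- **Primary and secondary endpoints:** among the secondary endpoints, "troponin T after 24 and 48 hours for determination of enzymatic infarct size will be evaluated".
- **Patient population:** eligibility requires "cardiac troponin levels above the 99th percentile" and "occurrence of previous symptoms less than 72 hours before randomization".
- **Data and statistical analysis, test:** "The differences in primary and secondary endpoints between the treatment groups will be assessed using an unpaired" t-test.
- **Data and statistical analysis, adjustment:** as a secondary analysis, "the differences between the treatment groups in the main outcome will be assessed using an unpaired" t-test with adjustment for baseline values, labelled ANCOVA. Only the main outcome is named for this.
- **Data and statistical analysis, subgroups:** one pre-specified subgroup splits patients at 6 hours from most recent symptoms to PCI, so this interval has to be recorded.

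**The concern.** Troponin T at 24 and 48 hours is meant to show whether aspiration limits the infarct. All patients already have raised troponin when they are randomized, and they may arrive at quite different times after onset. Release before the procedure cannot be altered by it. In an unadjusted comparison, differences between patients in that earlier release and in delay go into the error term.

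The two variables that could take some of this out are an entry troponin, which eligibility requires, and the symptom-to-PCI time, which the subgroup analysis requires. The plan uses neither for this endpoint. Its one adjusted analysis is for late microvascular obstruction, which is imaged once, on days 1 to 4, with no pre-treatment scan described. The marker that does have an entry value gets no adjustment.

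At stake is the sensitivity of one secondary endpoint. A modest effect on enzymatic infarct size is more likely to be missed, and its confidence interval will be wider than it need be.

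**Working it through.** **1. The plan's own figure.** For late microvascular obstruction the article takes a difference of 0.5 %LV, SD 1.8 %LV, two-sided 5% and 80% power:

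n per group = 2 × (1.960 + 0.8416)² × 1.8² / 0.5² = 2 × 7.849 × 12.96 = 203.4, rounded up to 204.

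This matches the stated 204. It does not bear on troponin, for which the article gives no effect, SD or power.

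**2. Inputs for troponin.**
- n = 230 per arm, from Randomization and patient treatment. The 10% loss in the sample-size section is for missing or unusable CMR, so it is not applied to blood samples.
- ρ, the correlation between log entry and log follow-up troponin, is not given. It is assumed at 0.1, 0.3, 0.5 and 0.7. The low values are included because patients sampled at different times after onset, or on different assays, may show only a weak correlation.

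**3. Formulas** (normal approximation, adjusted and unadjusted on the same scale).
- Residual variance factor: 1 − ρ².
- Difference detectable with 80% power, unadjusted: (1.960 + 0.8416) × √(2/230) = 2.8016 × 0.09325 = 0.261 SD.
- Detectable difference, adjusted: 0.261 × √(1 − ρ²).
- Power, adjusted, for the 0.261 SD effect: Φ(2.8016/√(1 − ρ²) − 1.960).
- Equivalent n per arm: 230/(1 − ρ²).

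| Assumed ρ | Variance removed | CI width, relative to unadjusted | Detectable difference (SD) | Power for 0.261 SD | Equivalent n per arm |
|---|---|---|---|---|---|
| 0 (unadjusted) | 0% | 1.00 | 0.261 | 80% | 230 |
| 0.1 | 1% | 0.995 | 0.260 | 80.4% | 232 |
| 0.3 | 9% | 0.954 | 0.249 | 83.6% | 253 |
| 0.5 | 25% | 0.866 | 0.226 | 89.9% | 307 |
| 0.7 | 49% | 0.714 | 0.187 | 97.5% | 451 |

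The table counts entry troponin only. Any further gain from symptom-to-PCI time is not included.

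**4. Is the unadjusted test biased?** Simulation with no treatment effect: 10,000 trials of 460 patients, each value the sum of an independent pre-randomization and post-randomization component, both lognormal with log-scale SD 1. The mean difference between arms was −0.004, in effect zero, and the unpaired t-test rejected in 4.7% of trials. The pre-randomization component adds noise but does not favour an arm.

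**The case against.** **The unadjusted comparison is legitimate.** Under central 1:1 randomization, earlier release and delay are balanced in expectation. A reader might infer that a chance imbalance in this unstratified trial could pass for a treatment effect. That is the ordinary 5% error, which the t-test already controls, as step 4 shows. This part of the objection stands in full: there is no bias to correct.

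**The size is unknown.** A reader might also infer that most of the 24 or 48 hour level was released before randomization. The article gives no troponin level, no distribution of delay and no pre-randomization share. A value above the 99th percentile may be only slightly raised, and 72 hours is an upper limit. This stands too: the part that predates treatment is real but unquantified, and at a correlation of 0.1 adjustment gains almost nothing.

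**Practicalities.** The eligibility criterion names cardiac troponin, not troponin T, and does not say that a numeric value is kept. Stored blood is described only for a single-center sub-study of about 200 patients, so a re-assay for everyone cannot be assumed. This limits the form of the fix but does not remove it.

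**Detail left to the full protocol.** The article does not say from when the 24 and 48 hours are counted. An article may leave that out, and nothing here rests on it. The test is different: the article states the unpaired t-test for secondary endpoints and names only the main outcome for ANCOVA. The univariate and multivariate regressions it also mentions serve to identify associated factors and are not presented as an adjusted troponin comparison.

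**Weight.** Infarct size is also measured by CMR with blinded reading, so troponin is not the only evidence on it. That keeps the point minor.

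**Conclusion.** The point holds as a matter of efficiency on a secondary endpoint. The article fixes an unadjusted comparison of a marker that is raised at entry in every patient, while the plan needs both an entry troponin and a symptom-to-PCI time for other purposes. Adjustment would remove between 1% and 49% of the variance for an assumed correlation of 0.1 to 0.7. Power for an effect detectable at 80% unadjusted would go from 80% to between about 80% and 97.5%.

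These figures rest on the assumed correlation, on 230 patients per arm with troponin measured, and on a usable entry value for each of them. They do not support a claim of bias, of inflated type I error, or that earlier release dominates the measurement. The primary analysis and the sample size are untouched.

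**What to change.** Make the main comparison of troponin T, at 24 hours and at 48 hours, an ANCOVA on log troponin T with two covariates: log entry troponin and time from symptoms to PCI. Where the entry assay was not troponin T, use the recorded entry value as a multiple of that assay's 99th percentile. Report the treatment effect as a ratio of geometric means with its 95% confidence interval. Keep the unadjusted t-test as a sensitivity analysis.

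State beforehand how a missing entry value is handled, so that no patient drops out of the comparison for lack of a covariate. Since almost 360 patients had been enrolled by December 2012, fix the wording before troponin is compared by arm.

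The cost is a change of analysis text and, if the numeric entry value is not already in the database, its retrieval from site records. Entry values may be missing or come from different assays in some patients, which would reduce the gain. No new sampling or re-assay is needed.

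### The follow-up re-infarction rule drops the marker-increase requirement of the in-hospital rule, so an early readmission with residual index troponin can count as a new infarction

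*Protocol article*

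**What the plan says.** The protocol article gives two re-infarction rules under Primary and secondary endpoints.

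- **Index stay.** "The diagnosis of re-infarction during the index hospitalization will be based on clinical symptoms, new ST-segment changes" and on a CK-MB criterion with two branches: "an increase in the creatine kinase-MB levels above the reference limits in patients with normalized values", or "an increase of more than 20% from the most recent non-normalized measurement".
- **Follow-up.** "any new ischemic symptoms leading to hospital admission accompanied by raised troponin levels will be defined as re-infarction". The sentence closes with a literature citation.

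Three other statements bear on the point.

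- Eligibility (Patient population) requires "cardiac troponin levels above the 99th percentile".
- The only scheduled troponin measurements are described as "troponin T after 24 and 48 hours for determination of enzymatic infarct size will be evaluated".
- Re-infarction is one component of the secondary outcome: "a combined clinical endpoint including death, re-infarction, target vessel revascularization, and congestive heart failure (CHF) will be assessed after 6 and 12 months".

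Events reported by telephone are checked against hospital or general practitioner records. A blinded Clinical Endpoints Committee (CEC) adjudicates all clinical endpoints.

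**The concern.** A single raised troponin shows new injury only if the marker had returned to normal beforehand. Here it is raised at entry in every patient, by design. The in-hospital rule deals with this by treating a marker that has not normalized differently from one that has. The follow-up rule makes no such distinction, and it takes over at discharge, not at normalization. Between discharge and normalization, the biomarker part of the definition is met automatically, and only the symptoms and the admission separate an event from a non-event.

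At stake is the specificity of one component of the combined clinical endpoint at 6 and 12 months. That endpoint matters to the trial's argument, because the article expects less microvascular obstruction to carry through to better clinical outcome. Falsely counted events that are equally frequent in both arms pull the relative risk toward 1.

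**Working it through.** **Comparison of the two rules**

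| Element | Index stay | Follow-up |
|---|---|---|
| Symptoms | Yes | Yes, new and ischemic |
| Admission | Not applicable | Yes |
| New ST-segment changes | Listed | Not listed |
| Marker | CK-MB | Troponin |
| Last value normal | Increase above the reference limits | Raised |
| Last value not normal | Increase of more than 20% | Raised |
| Minimum interval since index infarct | Not applicable | None |

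The in-hospital sentence can be parsed in more than one way, since its final clause may or may not stand apart from the symptoms and ST-segment changes. Every parsing still needs a marker increase. The follow-up sentence never does.

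Take ischemic chest pain with a marker that is falling but not yet normal. Before discharge it fails the in-hospital rule, because nothing has increased. On readmission shortly after discharge, with troponin falling but still raised, it meets the follow-up rule as written. The biology is the same in both cases; only the discharge date differs.

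**Size: an illustration on assumed figures**

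The article states no re-infarction rate, no readmission rate, no length of stay and no time to troponin normalization. There is therefore no stated figure to reproduce, and everything below is assumed except the 230 patients per arm (Randomization and patient treatment).

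Inputs: true control risk p0 of 5% or 10%; true relative risk 0.60; false-event probability f of 0%, 0.5%, 1% or 2% among patients without a true re-infarction, the same in both arms.

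Formulas:

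- observed control risk a = p0 + f(1 − p0)
- observed thrombectomy risk b = 0.6·p0 + f(1 − 0.6·p0)
- observed relative risk = b/a
- power: normal approximation for two proportions, 230 per arm, two-sided 5%, pooled variance under the null

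Example with p0 = 5% and f = 1%: a = 0.05 + 0.01 × 0.95 = 0.0595; b = 0.03 + 0.01 × 0.97 = 0.0397; b/a = 0.67. Expected false events are 230 × (0.0095 + 0.0097) = 4.4, against 230 × (0.05 + 0.03) = 18.4 true ones.

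| True risks | f | Observed risks | Relative risk | Power | False events in 460 |
|---|---|---|---|---|---|
| 5% v 3% | 0 | 5.00% v 3.00% | 0.60 | 19.3% | 0 |
| | 0.5% | 5.48% v 3.49% | 0.64 | 17.6% | 2.2 |
| | 1% | 5.95% v 3.97% | 0.67 | 16.3% | 4.4 |
| | 2% | 6.90% v 4.94% | 0.72 | 14.2% | 8.8 |
| 10% v 6% | 0 | 10.00% v 6.00% | 0.60 | 35.2% | 0 |
| | 0.5% | 10.45% v 6.47% | 0.62 | 33.5% | 2.1 |
| | 1% | 10.90% v 6.94% | 0.64 | 31.9% | 4.2 |
| | 2% | 11.80% v 7.88% | 0.67 | 29.1% | 8.5 |

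These figures are for re-infarction alone. In the composite, a patient falsely counted as a re-infarction may already count through revascularization, heart failure or death, so not every false re-infarction adds a composite event.

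**The case against.** **The article is condensed and cites a definition source.** The cited source, the full protocol or the CEC charter may require a rise in practice. That cannot be excluded. But the article does not leave the rule open: it states a complete operational definition, and that definition has no change criterion. The point is a rule fixed badly, not a missing detail.

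**The CEC will use judgment.** It may. A reader might infer that the committee is obliged to accept residual troponin as a new infarction, but the article says only that it adjudicates blinded, on data from the sites. Equally, blinding does not supply a criterion, and no other re-infarction criterion is printed for the committee.

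**Symptoms must be new, ischemic and lead to admission.** This is correct and it limits the problem. A raised troponin alone never counts, and the gap is confined to readmissions before troponin has normalized.

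**The rule is the same in both arms.** This also stands. Because the trial is open-label and discharge decides which rule applies, a reader might infer bias between the arms. Nothing in the article indicates that length of stay or readmission differs by arm, and adjudication is blinded. Dilution is what can be argued; differential bias is conjecture.

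**Safety monitoring.** A reader might suppose that false re-infarctions distort the counts seen by the Data Safety Monitoring Board. The article lists stroke and bleeding until discharge as the safety assessment and does not say that re-infarctions after discharge enter the board's counts.

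**A stricter rule could lose true events.** Scheduled troponins stop at 48 hours, so the last value before a late event may be raised or unknown. Records, possibly from a general practitioner, may hold a single sample. Requiring a serial rise throughout the 12 months could discard true late re-infarctions. This objection stands and shapes the fix.

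**Conclusion.** The concern holds in limited form. As written, the follow-up definition cannot separate residual index troponin from new injury in early readmissions, while the protocol's own in-hospital rule recognises and handles that situation. The gap shows from the text alone and depends on no assumed figure.

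Its size cannot be derived from the documents. With false events in 0.5% to 2% of patients without a true re-infarction, equal in both arms, a true relative risk of 0.60 would be observed as 0.62 to 0.72 across the two assumed control risks. Power for this component, already low, would fall by about 2 to 6 percentage points. A larger inflation of the event count would need an early readmission rate that the article does not give.

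The consequence is a modest dilution in one component of a secondary composite. The primary endpoint, late microvascular obstruction on CMR, and the sample size do not depend on it.

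**What to change.** Align the two definitions, for endpoint classification only.

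1. For a readmission where the last troponin was known to be raised, or within a prespecified early window after the index infarct, require a demonstrated increase over an earlier value. The window and the size of the increase should be fixed without sight of outcome by arm. The 20% figure in the present text applies to CK-MB, so its use for troponin should be an explicit decision.
2. Keep the current rule for later events. An unknown earlier value should not by itself trigger the stricter requirement outside the early window.
3. Have the blinded CEC apply this to the hospital or general practitioner records already obtained to verify each event.
4. Report early admissions without a demonstrable rise as a separate category, and add a sensitivity analysis of the composite that counts them as re-infarctions.

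The cost is one definition in the protocol and the CEC charter, with no change to treatment or visits. The re-infarction count will be slightly lower. Trial status reports almost 360 patients enrolled by December 2012, so early events already classified would need re-adjudication under the new wording. Some will lack serial values; the separate category and the sensitivity analysis show how much depends on them. The change should be documented as an amendment to a secondary endpoint made during the trial.
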